### Sample size {14}

Based on the primary endpoint analysis, the sample size was calculated as follows:

At the university hospital, LMU Munich, a delirium incidence of approx. 25% can be assumed for electively orthopedic surgery. By means of therapeutic suggestion may be reduced by at least 50%. The calculation in G*Power [24] using the z-test “Difference between two independent proportions” results in a sample size of 110 subjects per group for a design in which the intervention group and control group are of equal size, with a required power of at least 0.8 and a significance level of 5%. This results in a total of 220 subjects.

Based on the results of the study by Nowak et al. 2020 [11], we also calculated the sample size needed to detect effects of the intervention on pain expression, which are of great interest in the secondary endpoint analysis: For effects on opioid use, an effect size of *d* = 0.36 is assumed. For a required power of 0.8 at a level of significance at 5%, a group size of at least 101 subjects is needed. For effects on pain intensity, an effect size of 0.325 can be calculated using G*Power based on the mean values and standard deviations given in the original work. When power is set at 0.8 and significance level at 5%, the resulting sample size amounts to a total of 248 subjects.

In addition to the effect of the intervention on delirium incidence, the effect on pain severity is also of great interest as a (secondary) endpoint. Hence, the larger calculated sample number (*n* = 248) is chosen as a further basis for calculation to be able to achieve sufficiently good power for the secondary endpoints as well.

To ensure that the calculated minimum power will be achieved, there is a need to take possible drop-outs into account. Therefore at least 10% more subjects will be necessary, which results in a total of 273 participants. In consideration of the balanced design, the final target equals in a rounded up total number of 280 patients.

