### Statistical methods

#### Statistical methods for primary and secondary outcomes {20a}

To ensure normal distribution, the Kolmogorov–Smirnov test will be conducted prior to further analyses. Statistical significance will be considered at a *p*-value < 0.05. The primary outcome (postoperative delirium incidence) and other binary outcomes (e.g., incidence of postoperative nausea and vomiting, PONV) will first be compared between the intervention and control groups using the chi^2^ test. Continuous non-parametric variables will be analyzed with Mann–Whitney *U* tests, and parametric variables with Student’s *t*-test. To account for potential confounding effects of intraoperative and postoperative medication use, detailed data on the type and dosage of analgesics and sedatives will be collected. These variables will be included as covariates in multivariable logistic regression models for binary outcomes (e.g., delirium, PONV) and multivariable linear regression models for continuous outcomes (e.g., postoperative pain scores, NRS; intraoperative NOL index values). Confounders will be selected a priori based on clinical relevance and evidence from previous literature to avoid data-driven overfitting.

Medication-related parameters (e.g., total opioid dose, intraoperative sedative use) will also be analysed descriptively and compared between groups. Sensitivity analyses will be performed to assess the robustness of the results with and without adjustment for these covariates.

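### The three sample-size figures reproduce only with one-sided 5% tests (and 110 only with an unstated 12% delirium rate), so the planned chi-square test falls short of 80% power

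*Protocol article*

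**What the plan says.** Sample size {14} takes as its starting point that "a delirium incidence of approx. 25% can be assumed for electively orthopedic surgery". For the effect it says: "By means of therapeutic suggestion may be reduced by at least 50" per cent. The calculation is a G*Power z-test for two independent proportions with equal groups, "with a required power of at least 0.8 and a significance level of 5" per cent, and it "results in a sample size of 110 subjects per group", 220 in total.

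Two further calculations follow, both at power 0.8 and a 5% level. For opioid use at d = 0.36, "a group size of at least 101 subjects is needed". For pain intensity at an effect size of 0.325, "the resulting sample size amounts to a total of 248 subjects". The article adopts 248, adds 10% to reach 273 and rounds up to 280. It does not say whether any of these tests is one- or two-sided.

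Statistical methods {20a} sets the threshold at p < 0.05. The primary and other binary outcomes "will first be compared between the intervention and control groups using the chi^2^ test", and continuous outcomes are compared with Mann–Whitney U or Student's t-tests. No one-sided test is named. Objectives {7} words the hypotheses directionally, with lower values expected under the intervention.

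**The concern.** Halving 25% gives 12.5%, and 110 per group is too few to detect that difference with 80% power at a 5% level, whichever sidedness is used. All three printed figures look like the output of one-sided calculations, whereas a chi-square test of a 2×2 table at p < 0.05 is two-sided.

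If so, neither the primary endpoint nor the pain endpoint that fixes the final N has the stated power under the analysis as written. A non-significant delirium result would be read as coming from an adequately powered trial. With sidedness left open, it could also be settled after the data are seen.

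**Working it through.** **Inputs from {14}.** Control rate p1 = 0.25; a reduction of at least 50%, so p2 = 0.125 at the stated minimum; 1:1 groups; power 0.80; α = 0.05; effect sizes 0.36 and 0.325; 124 per arm (248/2); 140 per arm (280/2). If 10% of 280 are lost, 126 per arm remain.

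**Delirium, pooled z-test.** With p̄ the mean of p1 and p2,

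n per arm = [z_α √(2p̄(1−p̄)) + z_β √(p1(1−p1) + p2(1−p2))]² / (p1 − p2)²

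Here z_β = 0.8416, and z_α = 1.6449 one-sided or 1.9600 two-sided.

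*Reproducing 110.* With p2 = 0.12 the two square roots are 0.5491 and 0.5414, and (p1 − p2)² = 0.0169.
- One-sided: (1.6449×0.5491 + 0.8416×0.5414)² / 0.0169 = 109.3, so **110**, the printed figure.
- Two-sided: 138.9, so 139.

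*With the stated halving.* With p2 = 0.125 the square roots are 0.5520 and 0.5449, and (p1 − p2)² = 0.015625.
- One-sided: (0.9080 + 0.4586)² / 0.015625 = 119.5, so **120**.
- Two-sided: (1.0819 + 0.4586)² / 0.015625 = 151.9, so **152** (304 in total).

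Unpooled and arcsine versions give 118 one-sided and 150 two-sided. With a continuity correction the figures are 136 and 168. None gives 110.

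**Opioid use and pain.** The t-test requirement comes from the noncentral t distribution. The Mann–Whitney requirement is that number times π/3, the inverse of its asymptotic relative efficiency under normality.

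| Effect size | Test | One-sided n per arm | Two-sided n per arm | Printed |
|---|---|---|---|---|
| 0.36 | t | 96.1 → 97 | 122.1 → 123 | |
| 0.36 | Mann–Whitney | 100.6 → **101** | 127.9 → 128 | 101 per group |
| 0.325 | t | 117.7 → 118 (236 total) | 149.6 → 150 (300 total) | |
| 0.325 | Mann–Whitney | 123.3 → **124 (248 total)** | 156.6 → 157 (314 total) | 248 total |

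Both printed figures match the one-sided Mann–Whitney calculation exactly and no other entry in the table.

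**Power at the planned sizes.** For delirium,

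power = Φ{[(p1 − p2)√n − z_α √(2p̄(1−p̄))] / √(p1(1−p1) + p2(1−p2))}

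Example, 124 per arm, two-sided: (0.125×11.136 − 1.0819)/0.5449 = 0.569, and Φ(0.569) = 0.715.

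| n per arm | 25% v 12.5%, two-sided | Same, one-sided | 25% v 12%, two-sided |
|---|---|---|---|
| 110 | 0.663 | 0.770 | 0.702 |
| 124 | 0.715 | 0.813 | 0.754 |
| 126 | 0.722 | 0.818 | 0.760 |
| 140 | 0.767 | 0.853 | 0.803 |

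Exact binomial enumeration of the uncorrected chi-square test for 25% v 12.5% gives 0.669, 0.728, 0.725 and 0.773 down the rows. With Yates' correction it is 0.664 at 124 and 0.724 at 140.

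For pain at 0.325 and 124 per arm, two-sided power is 0.722 (t-test) or 0.702 (Mann–Whitney). One-sided it is 0.818 or 0.802.

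**What 80% two-sided power does cover.** For delirium from 25%: a reduction to about 11.3% (pooled formula) or 11.5% (exact) at 124 per arm, and to about 12% at 140. For pain at 124 per arm: an effect size of about 0.36 (t-test) to 0.37 (Mann–Whitney).

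**The case against.** The article never writes two-sided. Its hypotheses are directional, and three exact one-sided matches suggest a consistent one-sided design rather than three slips. A 2×2 comparison can be tested directionally through the signed root of chi-square, and the t and Mann–Whitney tests have one-sided forms. Read that way, the trial as sized meets its claim: for 25% against 12.5% one-sided power is 81% at 124 per arm and 85% at 140, and for pain it is 80–82% at 124. A rate of 12% is a 52% reduction, which fits a reduction of at least 50%. The operative target is 280, not 220, so the 66% at 110 per arm describes a trial nobody plans to run.

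Much of this stands. The shortfall depends on the two-sided reading, and the size to judge it by is 124 to 140 per arm. But a directional hypothesis does not declare a one-sided test, and a chi-square test at p < 0.05 does not perform one. The one-sided reading does not rescue 110 either: at the stated minimum effect it gives 77% power and 120 are needed. Sizing on 12% means that the stated minimum of 50% is not covered at 80% power.

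**Conclusion.** The concern holds. The figure of 110 per group does not follow from the printed inputs under either sidedness. Under {20a} as written, two-sided power for halving a 25% incidence is about 72% with 124 evaluable per arm and 77% if all 280 are analysed. Power for pain at 0.325 is 70–72% at 124 per arm. Two-sided requirements would be 304 in total for delirium and 300–314 for pain. Rounding up to 280 narrows the gap without closing it; 80% is reached two-sided only if the intervention rate is about 12% and nobody is lost.

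This rests on reading an unqualified chi-square test at p < 0.05 as two-sided and on the article's own 25% and effect sizes. If the control incidence were 20% or 15% (an assumption, not a figure from the article) with the same halving, exact two-sided power at 124 per arm would be about 61% or 47%.

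**What to change.** Make {14} and {20a} agree, without adding patients.

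- State the sidedness in both sections and print the intervention-group rate assumed.
- If testing is two-sided at 5%: remove the claim that 110 per group or 248 in total gives power of at least 0.8. Report that 25% against 12.5% has about 72% power with 124 evaluable per arm and 77% with 140. Report that 80% power applies to a reduction to about 11.3–11.5% (124 per arm) or about 12% (140 per arm). For pain, report 70–72% power at 0.325 with 124 per arm, and 80% at an effect size of about 0.36. Correct the opioid figure of 101 to 123 (t-test) or 128 (Mann–Whitney) per group.
- If one-sided 5% testing was intended: say so in {20a}, justify it and name a one-sided test for the primary outcome. Replace 110 with 120 per group for a 50% reduction, or state that 12% was assumed.
- Name the test behind the opioid and pain calculations.

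The cost is a rewording of the sample-size section and, for the one-sided option, of {20a}. With two-sided testing, the stated power becomes less favourable.

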## Recruitment {15}

At the LMU Munich university hospital, participants for the study will be recruited in the anesthesia outpatient clinic. If an eligible patient cannot be included in the anesthesia outpatient clinic, we will attempt to reach them through the orthopedics outpatient clinic.

### Assignment of interventions: allocation

#### Sequence generation {16a}

Included patients will be divided as follows: 1:1 (intervention vs. control group) and within the intervention group 1:1 to a speaker with the same gender (sGS) vs. a speaker with a different gender (dGS). Thus, the only factor influencing assignment is patient gender.

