## Methods: participants, interventions and outcomes

### Study setting {9}

All data will be collected in Germany. Leading center of the trial is the hospital of the Munich Ludwig-Maximilians-University (LMU). Further data is planned to be collected in the hospital of the Ruhr University Bochum as well as in the Heidelberg university hospital.

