*Now shift your attention back from the inside to the outside. See the light, hear the sounds, you become more and more alert and start moving again. You can orient yourself and find your way around. Everything is fine.*

As soon as the propofol application is being stopped to wake up the patient, headphones will be removed. This is considered the end of our intervention. As the trial is double blinded, patients in the control group are presented with two different audio tracks as well, but these are empty tracks. For patients of all groups, there will be no background music withing the audio tracks.

Apart from the audio exposure, perioperative management will be identical in all groups: Anesthesia will be administered as total intravenous anesthesia (TIVA) using propofol for induction and maintenance, combined with sufentanil for intraoperative analgesia. Neuromuscular blockade will be achieved with rocuronium as needed. Depth of anesthesia will be monitored using bispectral index (BIS) monitoring. Standard multimodal analgesia, perioperative antibiotic prophylaxis, and postoperative nausea and vomiting (PONV) prophylaxis (dexamethasone and ondansetron, unless contraindicated) will be provided according to institutional protocols. No other aspects of anesthesia care will differ between study arms.

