#### Implementation {16c}

Trained junior researchers will enroll participants, while the allocation sequence will be automatically generated by RedCap. In detail, randomization will be conducted in REDCap using permuted block randomization with stratification by gender, resulting in separate randomization lists for male and female participants. This ensured a balanced allocation between intervention and control groups within each gender. The gender stratification was implemented to allow for the preplanned secondary analysis of potential effects related to gender–voice congruence. The PI of the study will perform randomization in the above mentioned way.

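### Hospital is used neither in the allocation nor in the stated comparisons of this three-hospital trial, which costs a little precision (minor)

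*Protocol article*

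**What the plan says.** Study setting {9} names Munich as the lead hospital and adds: "Further data is planned to be collected in the hospital of the Ruhr University Bochum as well as in the Heidelberg university hospital". The sections on auditing and the Discussion also call the trial multicentre, and the Discussion counts this as a strength.

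Implementation {16c} describes "permuted block randomization with stratification by gender, resulting in separate randomization lists for male and female participants". Sequence generation {16a} closes the matter: "Thus, the only factor influencing assignment is patient gender". No list per hospital is described.

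Intervention description {11a} names the anaesthetic technique and the default antiemetics for everyone. Standard multimodal analgesia, antibiotic prophylaxis and PONV prophylaxis, however, "will be provided according to institutional protocols".

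Statistical methods {20a} gives a chi-squared test for delirium and PONV, and t or Mann-Whitney tests for continuous outcomes. Regression models follow, and the covariates they name are medication variables. Further confounders are to be chosen in advance, and hospital is not mentioned.

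**The concern.** Where analgesia and antiemetic practice follow the hospital, hospital is a plausible predictor of pain scores, analgesic consumption and PONV, which are all secondary hypotheses. Pain intensity also set the sample size, because its total of 248 was preferred to 220. With one list for men and one for women serving all hospitals, 1:1 balance holds within gender but not within hospital. If the arms end up with different hospital mixes, part of the hospital difference enters the treatment comparison as random error. Stratifying on hospital, or adjusting for it, would remove that error. The same holds for the voice-congruence comparison, where each half is only a quarter of the sample.

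**Working it through.** **Inputs from the article.** The target is reached as 248 x 1.10 = 272.8, given as 273; then "the final target equals in a rounded up total number of 280 patients". This gives 140 per arm and 70 per voice half. Planned d for pain intensity is 0.325. Delirium is assumed to fall from 25% by half, to 12.5%.

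**Assumptions (not in the article).** Hospital shares, differences between hospitals, hospital-specific delirium rates, blocks of 4, and patients from the hospitals arriving in mixed order. If a hospital recruits in long uninterrupted runs, the blocks give it more balance than shown here.

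**1. Split within a hospital** (hypergeometric draw from 140/140).
- A hospital with 40 patients has a 23% chance of a 60:40 or worse split between intervention and control. With 56 patients the chance is 10%.
- Among 20 intervention patients in one hospital (drawn from 70/70), the two voice halves split 12:8 or worse with probability about 47%, and 13:7 or worse about 23%.

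**2. Difference between arms in the share s of patients from outside the lead hospital.** SD = 2 x sqrt(s(1-s)/279).
- s = 0.2: 2 x sqrt(0.16/279) = 0.048; x 1.96 = 0.094.
- s = 0.4: 2 x sqrt(0.24/279) = 0.059; x 1.96 = 0.115.

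The 95% range is therefore about ±9 to 11 points. In simulation with a 60/20/20 mix, some hospital's share differs by 10 points or more in 12-13% of trials, and the 95th percentile of the largest difference is 12.1 points. With gender-by-hospital lists these become about 0 and 1.9 points.

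**3. Continuous outcomes, hospital difference 0.5 SD.**
- 95% limit of the contribution to the estimate: 0.5 x 0.094 = 0.047 and 0.5 x 0.115 = 0.0575.
- Half-width of the interval for d without it: 1.96 x sqrt(2/140) = 0.234.
- Combined: sqrt(0.234² + 0.047²) = 0.239 and sqrt(0.234² + 0.0575²) = 0.241, which is 2% and 3% wider.
- Check by variance: sqrt(1 + 0.16 x 0.25) = 1.02 and sqrt(1 + 0.24 x 0.25) = 1.03.
- At a 1 SD difference: sqrt(1.16) = 1.08 and sqrt(1.24) = 1.11, which is 8-11% wider.

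**4. Adjusting without stratifying.** The expected loss against stratified allocation with the same model is roughly (k-1)/(N-1) = 2/279 = 0.7%. Nearly all of the gain comes from the analysis.

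**5. Delirium** (4000 simulated trials per scenario, two-sided 5%; hospital rates 25/15/35% or 25/10/40%).
- Type I error of the unadjusted test: 4.3-5.4% over mixes of 33/33/33, 60/20/20 and 80/10/10.
- 95th percentile of the shift in expected risk difference: 1.1-2.8 points, against a standard error of sqrt(0.25 x 0.75 x 2/140) = 5.2 points and an assumed effect of 12.5 points.
- Power at 60/20/20: 76.6-77.0% with gender-only lists and the unadjusted test; 78.0-78.5% with hospital-stratified lists and a hospital-stratified test. Each figure has a simulation error of sqrt(0.77 x 0.23/4000) = 0.7 points, so the gain is known only as roughly 1-2 points.

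**The case against.** The strongest reply is that randomisation is valid without hospital as a stratum, that gender was chosen because the voice question needs it, and that the cost is small. All of that stands.

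It also stands that differing hospital protocols are inferred. The article shows no difference, fixes much of the anaesthetic regimen for every patient, and says under {21a} that the centres agreed a unified basis for conduct. The remark "At the university hospital, LMU Munich, a delirium incidence of approx. 25% can be assumed" gives one hospital's rate and does not show that the others differ. The planned d comes from a trial that the article describes as multicentre, so its SD may already contain variation between centres. The analysis plan is not shown, and choosing confounders in advance does not exclude hospital.

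What survives is narrower. The allocation factor is stated outright, so an unseen analysis plan cannot alter it, and the comparisons that the article does describe make no use of hospital.

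A reader might infer three stronger things that the documents do not support:
- **That the promise of equal perioperative management fails.** That statement compares study groups. Within a hospital both arms follow the same protocol, so it holds.
- **That a small hospital becomes nearly uninformative.** A 60:40 split keeps 4 x 0.6 x 0.4 = 96% of the information of an even split, and no hospital-specific analysis is planned.
- **That the pain effect may be distorted by 14-18%.** That is 0.047 to 0.0575 divided by 0.325. It is the 95% extreme of one component of ordinary sampling error, and its effect on the interval is the 2-3% shown above.

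**Conclusion.** The point holds as a minor loss of precision. Hospital mix can differ between arms and between voice halves by chance, and neither the allocation nor the stated comparisons deal with it. This does not bias the comparison on average, and type I error stays near 5%.

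For pain and analgesic use the interval for d is about 2-3% wider, given 20-40% of patients outside the lead hospital and a 0.5 SD hospital difference. A 1 SD difference would make that 8-11%, but nothing in the documents suggests a difference of that size. For delirium about 1-2 points of power are at stake under the assumed hospital rates. If the hospitals' practice is in fact uniform, the loss is close to nil.

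**What to change.** Before unblinding, specify hospital as a factor, together with gender, in the regression models for NRS, analgesic consumption, NOL and PONV. For delirium, use a hospital-stratified test (for example Mantel-Haenszel) or a hospital-adjusted comparison. Hospital is known for every patient at baseline, so this costs a sentence in the analysis plan and two degrees of freedom.

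Enrolment has run since November 2022, with data collection expected to end in October 2025, so patients already randomised cannot be re-stratified. For any hospital not yet open or still recruiting, load centre-by-gender lists in REDCap from the next patient (six lists in all, with the same 1:1 and nested 1:1 ratios). That needs new allocation tables and a short amendment, and leaves slightly more incomplete blocks. No extra patients are needed. If little recruitment remains, the analysis factor alone is enough.

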#### Concealment mechanism {16b}

Numbered audio players will be used to maintain blinding of the trained junior researchers conducting the intervention and data collection. After the randomization process, the study’s PI will notify the relevant parties regarding the designated number of the audio player to be utilized.

Those administering the intervention as well as the anesthetists in charge will not have permission to listen to the audio tracks on the different audio players.

#### Implementation {16c}

Trained junior researchers will enroll participants, while the allocation sequence will be automatically generated by RedCap. In detail, randomization will be conducted in REDCap using permuted block randomization with stratification by gender, resulting in separate randomization lists for male and female participants. This ensured a balanced allocation between intervention and control groups within each gender. The gender stratification was implemented to allow for the preplanned secondary analysis of potential effects related to gender–voice congruence. The PI of the study will perform randomization in the above mentioned way.

